### National Institute of Health Stroke Scale

The NIHSS, or NIH Stroke Scale is a tool used by healthcare providers to objectively quantify the impairment caused by a stroke, but has been used extensively for outcome in glioma surgery because of the lack of such scale for neuro-oncological purposes and has been validated. The NIHSS is composed of 11 items, each of which scores a specific ability between a 0 and 4. For each item, a score of 0 typically indicates normal function in that specific ability, while a higher score is indicative of some level of impairment. The individual scores from each item are summed in order to calculate a patient’s total NIHSS score. The maximum possible score is 42 and the minimum score 0.

### Aphasia bedside check

ABC is a short screening test to detect aphasic disturbances at language comprehension and language production level at the main linguistic levels. It consists of 14 items in total. The cut-off score for signs of aphasia is ≤12.

### Shortened Token Test

The shortened Token Test is a test for language comprehension and for the severity of a language disorder. The patient is asked to point and to manipulate geometric forms on verbal commands. It consists of 36 items. The cut-off score is 29.5.

### Verbal fluency (category and letter)

Category and letter fluency are tests to assess flexibility of verbal semantic and phonological thought processing, semantic memory and concept generation. The patients is asked to produce words of a given category (animals, professions) or beginning with a given letter (D, A, T) within a limited time span.

### Picture description and object naming

The picture description test, a subtest from the CAT-NL (Comprehensive Aphasia Test-Netherlands), is used to assess semispontaneous speech in an oral and written way (5 min each condition). Scoring can be done according to the manual or more thoroughly according to the variables mentioned by Vandenborre *et al*.^22^ To assess word retrieval, various object naming tests are used: BNT (Boston Naming Test), DuLIP (Dutch Linguistic Intraoperative Protocol) and VAN-POP (Verb and Noun test for Perioperative Testing).

### Montreal Cognitive Assessment

The MOCA is a cognitive screening test to detect mild impairments across several cognitive domains; attention, verbal memory, language, visuoconstructive skills, conceptual thought, calculation and orientation. The total score is 30, the cut-off score is ≤26.

### EQ-5D

The EQ-5D is a standardised questionnaire to assess the general HRQoL in five domains: mobility, self-care, usual activity, pain/discomfort and anxiety/depression. It is developed by the EuroQol Group and can also be used to calculate quality-adjusted life years for cost–utility analyses.

### QLQ-C30 and QLQ-BN20

The QLQ-C30 and QLQ-BN20 are standardised questionnaires that have been designed by the Euoprean Organisation for Research and Treatment of Cancer (EORTC). They are used to assess the quality of life in cancer patients in general (C30) and brain tumor patients (BN20) by incorporating functional scales (physical, role, cognitive, emotional, social) and symptom scales (fatigue, pain, nausea and vomiting, seizures, communicating).

### Sample size

This study has two primary endpoints. In order to guarantee that the overall type I error rate does not exceed 5%, we apply a weighted Bonferroni correction for multiple testing. The sample size calculations that follow take that into account. For the first primary endpoint, proportion of patients with neurological deterioration at 6 weeks postsurgery, we assume a deterioration rate of 10% in the control group (arm 3: no mapping), and 3% in the experimental groups (arm 1 and 2: awake and asleep mapping). A two-sample test for proportions with continuity correction requires 411 patients (137 per arm) in total in order to detect the above-mentioned difference of 7% with 80% power at a 4% significance level. For the second primary endpoint, proportion of patients without residual contrast-enhancing tumour on postoperative MRI, we assume a success rate of 25% in the control group (arm 3: no mapping), and 50% in the experimental groups (arm 1 and 2: awake and asleep mapping). A two-sample test for proportions with continuity correction requires 188 patients (94 per arm) in total in order to detect the above-mentioned difference of 25% with 80% power at a 1% significance level. In order to power the study for both primary endpoints, we should include the larger required number of patients, that is, 411. A total of 411 eligible and evaluable patients in three arms allow the difference of 25% in proportion of patients without residual tumour to be detected with 88% power. Taking into account possible ineligibility and withdrawal of consent (we estimate this at 10%), a total of 453 patients will be included (151 patients per arm).

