## Methods and analysis

### Study design

This is a international, multicenter, prospective, three-arm cohort study. Eligible patients are operated using awake mapping, asleep mapping or no mapping with a 1:1:1 ratio with a sequential computer-generated random number as subject ID. Patients with motor-eloquent tumours will be treated in all study arms, while speech-eloquent tumours will only be treated in either the awake mapping or no mapping arm. The PROGRAM study (prospective cohort study of high-grade glioma resections using awake craniotomy and intraoperative stimulation mapping) is similar to the SAFE-trial (SAFE surgery for glioblastoma patients: awake craniotomy versus craniotomy under general anesthesia: a multicenter randomized controlled trial) and is initiated by the same center, however, the presented study will be different in various ways: the PROGRAM study (1) will be an observational, prospective cohort study, (2) will include asleep mapping as an additional treatment arm, (3) will evaluate the extent of resection of the non-contrast-enhancing part of the tumour as well, (4) will include both WHO grade III and grade IV gliomas, (5) will include an oncofunctional score as one of the outcomes and (6) will include neurosurgical centers in the USA and is part of the ENCRAM Research Consortium.^18^

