### Primary study parameters

The primary endpoints will be analysed using multivariate logistic regression. Subgroup analyses for tumour grade (WHO grade III/IV), preoperative neurological morbidity, preoperative tumour volume, patient’s age (in 10-year age brackets) and tumour location/eloquence will be performed.

We will be including a stratification factor in the primary analysis model with each 10 observed events using the order of prognostic value as mentioned in the paragraph above, where the first 10 events will be used to estimate the effect of the arm. This rule will be applied in case less than 40 patients in total develop neurological deterioration. In the so constructed multivariate logistic regression model the treatment arm effect will be tested at 4% significance level. The primary analysis of proportion of patients without residual contrast-enhancing and non-contrast-enhancing tumour consist of a multivariate logistic regression, where arm effect is corrected for all minimisation factors. In this model the group effect will be tested at 1% significance level. Manual or semiautomatic segmentation will be performed on axial T1 and T2/FLAIR MRI contrast enhanced slices to measure preoperative and postoperative tumour volume. A determination of volumes will be calculated blinded for the treatment group.

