## Discussion

Neurosurgeons face a major dilemma during glioma surgery: maximising extent of resection while minimising risk of postoperative neurological deficits. The use of awake or asleep mapping techniques has the potential to equip the surgeon intraoperatively with the needed information to balance these two surgical goals.

A substantial amount of evidence is available on the usefulness of awake mapping to increase resection percentage while preserving quality of life in LGG patients.^23–34^ In contrast, only very few studies have reported the use of awake mapping in HGG patients, although this technique could be of important value in these patients as well.^17 23 25–27 34^ Recent retrospective evidence showed that glioblastoma patients operated with awake mapping had significant less postoperative neurological morbidity and significantly higher percentage of total resections.^35 36^ In patients with motor-eloquent tumours, the use of asleep mapping techniques with evoked potentials or CDM can be a viable alternative to preserve these functional tracts.^20 37 38^

There is a clear need for solid prospective evidence of the use of these techniques in HGG patients. The presented international neurosurgical research consortium will provide the needed infrastructure to perform ongoing large-scale data collection.^18^ This study aims to evaluate whether the use of awake or asleep mapping is the appropriate answer to the surgeon’s surgical dilemma during HGG resections. Furthermore, it will be the first to directly compare awake and asleep mapping techniques in their ability to improve patient outcomes for neurological morbidity, quality of life and survival. Last, using various multivariate analyses, there will be an additional focus on identifying the best surgical choice in subgroups of HGG patients.

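### The 4% + 1% split keeps the overall type I error at 5% only with one confirmatory arm test per endpoint, and the protocol does not fix which test that is

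*Protocol article*

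**What the plan says.** All places are in the protocol article.

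- **Sample size, error rate.** The section opens with "This study has two primary endpoints" and continues: "In order to guarantee that the overall type I error rate does not exceed 5%, we apply a weighted Bonferroni correction for multiple testing". The split is 4% for endpoint 1 (deterioration at 6 weeks) and 1% for endpoint 2 (no residual contrast-enhancing tumour). The number of arms is not mentioned in this connection.
- **Study design.** There are three arms: "Eligible patients are operated using awake mapping, asleep mapping or no mapping with a 1:1:1 ratio".
- **Sample size, endpoint 1.** "we assume a deterioration rate of 10% in the control group (arm 3: no mapping), and 3% in the experimental groups". Then: "A two-sample test for proportions with continuity correction requires 411 patients (137 per arm) in total", to detect a "difference of 7% with 80% power at a 4% significance level".
- **Sample size, endpoint 2.** 25% against 50%, 80% power at 1%, giving 188 patients, 94 per arm. Since 188 = 2 × 94, this counts two arms only.
- **Primary study parameters.** One logistic model per endpoint. For endpoint 1, "the treatment arm effect will be tested at 4% significance level". For endpoint 2 the corresponding single effect is tested at 1%. Neither effect is defined as pooled, 2-df or pairwise.
- **Discussion.** The study is presented with the words "it will be the first to directly compare awake and asleep mapping techniques". The strengths list after the abstract likewise describes a direct comparison of all three approaches.

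Sidedness is not stated for either endpoint.

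**The concern.** A weighted Bonferroni split over two endpoints protects two tests. With three arms, one endpoint can give rise to two tests (each mapping arm against no mapping) or three (adding awake against asleep). Nothing is left of the 5% for these, and no order or gate for testing them is given.

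This matters because the article states the 5% as a guarantee and also announces conclusions about individual techniques. A statement that awake mapping beats no mapping, or that it beats asleep mapping, is a pairwise claim. Whether it is covered by the guarantee depends on what the arm effect means, and the article's own figures point in different directions on that.

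**Working it through.** **Step 1: reproduce the stated error rate.** 4% + 1% = 5%. This is a valid bound for exactly one test per endpoint.

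**Step 2: reproduce the sample sizes, to see which contrast they imply.** For n controls and k·n in the comparison group, with d = |p1 − p2| and p̄ = (p1 + k·p2)/(1 + k):

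n0 = [z_α·√(p̄(1 − p̄)(1 + 1/k)) + z_β·√(p1(1 − p1) + p2(1 − p2)/k)]² / d²

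With continuity correction: n = (n0/4)·[1 + √(1 + 2(1 + 1/k)/(n0·d))]²

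*Endpoint 1* (0.10 against 0.03, 80% power, 4%). Pooled mapping, k = 2, one-sided: p̄ = 0.16/3 = 0.0533, z_α = 1.751, z_β = 0.842. This gives n0 = 116.0 and n = 136.6, rounded up to 137 controls. Mapping = 2 × 137 = 274, total 411, as stated.

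*Endpoint 2* (0.25 against 0.50, 80% power, 1%). Two arms, k = 1, two-sided: p̄ = 0.375, z_α = 2.576. This gives n0 = 86.1 and n = 93.97, rounded up to 94. Total 2 × 94 = 188, as stated.

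Control-group size for each combination, with continuity correction:

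| Contrast | Endpoint 1 at 4% (stated 137) | Endpoint 2 at 1% (stated 94) |
|---|---|---|
| Pooled 2:1, one-sided | **137** | 63 |
| Pooled 2:1, two-sided | 164 | 72 |
| Pairwise 1:1, one-sided | 194 | 82 |
| Pairwise 1:1, two-sided | 235 | **94** |

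The two endpoints are therefore sized for different contrasts and different sidedness.

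**Step 3: overall error under each reading, all null hypotheses true, equal arms, two-sided tests, normal approximation.**

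*One pooled or one 2-df test per endpoint:* at most 4% + 1% = 5%.

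*Each mapping arm against no mapping, no gate.* The shared control gives the two statistics a correlation of 0.5. The chance of at least one rejection is 1 − P(|Z1| ≤ c and |Z2| ≤ c):
- c = 2.054 (4%): 7.3%
- c = 2.576 (1%): 1.9%
- independent endpoints: 1 − (1 − 0.0732)(1 − 0.0190) = 9.1%
- whatever the dependence between endpoints: at least 7.3% (the larger of the two) and at most 7.3% + 1.9% = 9.2%

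Simulated binary data with 137 per arm gave 7.4%, 1.8% and 9.0%.

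*All three pairs, no gate* (studentized range, three groups, critical value c·√2): 10.0% and 2.7%. With independent endpoints, 1 − (1 − 0.0997)(1 − 0.0270) = 12.4%. By sum, 12.7%.

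*Pairwise tests allowed only after the 2-df test rejects at the same level.* If all three arms are equal, any rejection must first pass the gate, which has probability 4% (or 1%). If only one pair is equal, there is one true pairwise null and it is tested at 4% (or 1%). With three arms there is no other case, so each endpoint keeps its level and the total stays at 5%.

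**Step 4: what 137 per arm delivers under each contrast.** Unadjusted; cc = continuity correction.

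| Contrast | Endpoint 1 at 4% | Endpoint 2 at 1% |
|---|---|---|
| Pooled, one-sided | 80% (cc) | over 99% |
| Pooled, two-sided | 78%; 72% (cc) | 99% |
| 2-df arm test | 73% | 97% |
| Pairwise, two-sided | 62%; 52% (cc) | 96%; 95% (cc) |

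The article's 88% power for endpoint 2 with 411 patients matches none of these, so it does not help to identify the contrast.

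**The case against.** The strongest reply is that the planned tests keep the guarantee. The analysis section names one effect per endpoint, at exactly 4% and 1%. The figure that sets the study size, 411, fits one pooled contrast. The objectives are framed as resection with or without mapping, which is a mapped-against-unmapped question. The awake-against-asleep remark stands in the Discussion, covers quality of life and survival as well, and carries no hypothesis or significance level. Details of pairwise follow-up are often left to the analysis plan.

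Most of this stands. A reader might infer that the 5% guarantee fails, or that two or three confirmatory contrasts per endpoint are planned. The document supports neither: no section makes awake against none, asleep against none, or awake against asleep a separate primary test. The 9% and 12% describe ungated testing that the article leaves open, not a procedure it prescribes.

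The reply does not settle which contrast is primary. The endpoint 2 sizing fits a two-arm comparison, not a pooled one. This is also more than a detail left to another document: the article itself fixes the guarantee, the split, the two sizings and the test levels, and these do not refer to one common contrast.

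**Conclusion.** The point holds as a statement about an unfixed primary contrast. The 5% bound is correct for one pooled or one 2-df test per endpoint, and it is silent on any arm-specific or awake-against-asleep claim. If each mapping arm were tested against no mapping at 4% and 1% without a gate, the overall error would be about 9% (7.3% to 9.2%, depending on how the endpoints are related). With all three pairs it would be about 12% (at most 12.7%).

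These figures assume equal arms, two-sided unadjusted tests, all nulls true, and each endpoint taken as the single outcome used in the Sample size section. The 9.1% and 12.4% also assume independent endpoints. The statement that 411 fits only the pooled one-sided contrast refers to the combinations in the table, at 4% with the standard continuity-corrected formula.

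The point should be settled before analysis. It does not invalidate the design.

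**What to change.** State the same confirmatory test in the Sample size and Primary study parameters sections, in one of two ways:

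1. The confirmatory test for each endpoint is the 2-df arm test, at 4% and 1%. Pairwise contrasts are tested at the same level only if it rejects. With three arms this is a closed procedure and needs no further split.
2. Pooled mapping against no mapping is the only confirmatory contrast for each endpoint. Arm-specific and awake-against-asleep comparisons are descriptive.

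In either case, state the sidedness and restate sample size and power for both endpoints on the chosen contrast, including the 88%.

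**Cost.** For error control, wording only. Under option 1 no confirmatory pairwise claim is possible when the gate does not reject. Under option 2 none is possible at all. The stated power for endpoint 1 may fall: with 137 per arm it is about 73% for the 2-df test and 72% for a two-sided pooled test with continuity correction, against the 80% planned. Dividing the levels between two separate ungated contrasts would cost far more. Bonferroni at 2% per contrast needs 276 per arm for endpoint 1 (828 in total), and Dunnett at about 2.14% needs 272 per arm (816), both two-sided with continuity correction.

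### The fixed 4%/1% weighted Bonferroni split is valid, but weighted Holm with the same weights gives more power at the same 5% familywise level

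*Protocol article*

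**What the plan says.** The Sample size section of the protocol article names two primary endpoints and gives the reason for the adjustment: "In order to guarantee that the overall type I error rate does not exceed 5" per cent. The method is stated as "we apply a weighted Bonferroni correction for multiple testing".

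The design levels follow from it. Endpoint 1 (neurological deterioration at 6 weeks) is sized for "the above-mentioned difference of 7% with 80% power at a 4% significance level". Endpoint 2 (no residual contrast-enhancing tumour) is sized for "the above-mentioned difference of 25% with 80% power at a 1% significance level".

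The section Primary study parameters carries the same levels into the analysis. For endpoint 1, "the treatment arm effect will be tested at 4% significance level". For endpoint 2, "In this model the group effect will be tested at 1% significance level". Nothing in the article passes the level of a rejected endpoint to the other one.

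**The concern.** The article fixes both test levels itself, so this is a stated choice and not a detail left to an analysis plan. Under that choice, 1% of alpha stays with endpoint 2 after endpoint 2 has succeeded, and 4% stays with endpoint 1 after endpoint 1 has succeeded. Holding it there no longer protects anything. Weighted Holm releases it to the remaining test.

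The probability of winning on at least one endpoint is the same under both procedures. The fixed split therefore loses only on the second endpoint. For example, with p = 0.01 for deterioration and p = 0.02 for residual tumour, the plan must call the resection result negative, although 5% familywise control would allow it to be called positive.

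**Working it through.** **Inputs** (Sample size section). Endpoint 1: "we assume a deterioration rate of 10% in the control group (arm 3: no mapping), and 3% in the experimental groups". Endpoint 2: "we assume a success rate of 25% in the control group (arm 3: no mapping), and 50% in the experimental groups". Levels 4% and 1%; 411 patients, 137 per arm; two-sample tests of proportions with continuity correction. The article does not state sidedness, or whether the mapping arms are pooled.

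**Level.** 0.04 + 0.01 = 0.05, so the split does what it claims.

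**The plan's own figures** (pooled-variance formula with continuity correction).
- 411: one-sided 4%, 80% power, 137 controls v 274 pooled mapping patients gives 116 controls uncorrected and 137 corrected; 3 × 137 = 411. It reproduces. A two-sided test would need 164 controls (492 in total) at 2:1, or 235 per arm at 1:1.
- 188: two-sided 1%, 1:1, gives 87 per arm uncorrected and 94 corrected; 2 × 94 = 188. It reproduces.
- 88% power for endpoint 2 at 411: does not reproduce. The two-sided corrected formula gives 94.8% for 137 v 137 and 99.0% for 137 v 274.

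**Why Holm keeps 5%.** If both nulls are true, a false rejection must start with p1 ≤ 0.04 or p2 ≤ 0.01, which has probability at most 0.04 + 0.01 = 0.05 under any dependence. If only one null is true, falsely rejecting it needs its own p ≤ 0.05.

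**Power.** Let a4 and a5 be endpoint 1 power at 4% and 5%, and b1 and b5 endpoint 2 power at 1% and 5%. For independent endpoints:
- endpoint 1: a4 under Bonferroni; a4 + b1(a5 − a4) under Holm
- both: a4·b1 under Bonferroni; b1·a5 + a4(b5 − b1) under Holm

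Worked case, 137 v 274, both tests two-sided and corrected, marginal powers summed exactly over the binomial distributions: a4 = 0.7396, a5 = 0.7612, b1 = 0.9897, b5 = 0.9984.
- both, Bonferroni: 0.7396 × 0.9897 = 0.732
- both, Holm: 0.9897 × 0.7612 + 0.7396 × 0.0087 = 0.760
- endpoint 1, Holm: 0.7396 + 0.9897 × 0.0216 = 0.761

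Worked case, 137 v 137, same tests: a4 = 0.5368, a5 = 0.5723, b1 = 0.9495, b5 = 0.9885.
- both, Bonferroni: 0.5368 × 0.9495 = 0.510
- both, Holm: 0.9495 × 0.5723 + 0.5368 × 0.0390 = 0.564
- endpoint 1, Holm: 0.5368 + 0.9495 × 0.0355 = 0.571

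Endpoint 2 is two-sided in every row below. The first six rows are exact binomial sums. The seventh uses the formula that reproduces 411 (a4 = 0.8012, a5 = 0.8253, b1 = 0.9903, b5 = 0.9987).

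| Comparison, endpoint 1 test | Endpoint 1, % | Both, % | Gain, both |
|---|---|---|---|
| 137 v 274, two-sided, corrected | 74.0 to 76.1 | 73.2 to 76.0 | 2.8 |
| 137 v 137, two-sided, corrected | 53.7 to 57.1 | 51.0 to 56.4 | 5.4 |
| 137 v 274, two-sided, uncorrected | 79.8 to 83.0 | 79.2 to 82.9 | 3.7 |
| 137 v 137, two-sided, uncorrected | 64.3 to 67.3 | 61.8 to 66.7 | 4.9 |
| 137 v 274, one-sided, uncorrected | 87.5 to 88.9 | 86.8 to 88.8 | 2.0 |
| 137 v 137, one-sided, corrected | 65.5 to 69.3 | 62.2 to 68.5 | 6.3 |
| 137 v 274, one-sided, corrected (formula) | 80.1 to 82.5 | 79.3 to 82.4 | 3.1 |
| Stated powers of 80% and 88%, two-sided | 80 to 82.2 | 70.4 to 79.3 | 8.9 |

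Endpoint 2 itself gains under 1 point for 137 v 274 (99.0% to 99.6%, first row) and about 2 points for 137 v 137 (95.0% to 97.0%, second row). Correlations from −0.5 to 0.5 move the endpoint 1 gain by less than 0.2 points in the main scenarios.

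**The case against.** The strongest reply is that nothing here is wrong. Weighted Bonferroni is valid, it is pre-specified, the sample size accounts for it, and the analysis section applies the same levels. That stands: this is avoidable inefficiency, and a reader should not infer that type I error is inflated.

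Fixed levels also have a real advantage. The 96% and 99% intervals match the test decisions exactly, which matters in a non-randomised cohort where estimates count for at least as much as tests. That stands too, as the one cost of changing.

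Three stronger readings are tempting, and the article does not support them.
- *The gain is 9 points for both endpoints, with endpoint 2 rising from 88% to 95%.* This rests on the stated 88%. At the planning rates endpoint 2 already has about 95% or 99% power at 1%, so little is left to gain there. A significant endpoint 1 with a residual-tumour p-value between 0.01 and 0.05 would occur in only about 0.6% of studies (137 v 274) or 2% (137 v 137), two-sided and corrected.
- *With Holm, 411 becomes conservative.* With two-sided corrected tests endpoint 1 reaches only about 76% (137 v 274) or 57% (137 v 137), even under Holm.
- *The study succeeds only if both endpoints are significant.* Study objectives says that safety and efficacy will be evaluated; it sets no such rule. If both were required, each could be tested at the full 5% and no split would be needed. On the stated powers that gives 0.825 × 0.963 = 79.5%, against 79.3% for Holm.

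**Conclusion.** The point holds as a minor, optional improvement. The fixed 4%/1% split controls error at 5% but is uniformly less powerful than weighted Holm with the same weights. That ordering is mathematical and does not depend on the planning assumptions.

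The size does depend on them. With the planning rates, 411 evaluable patients, independent endpoints and the two-sample tests used for planning (not the adjusted logistic models), the gain is about 2 to 6 points for winning on both endpoints and about 1 to 4 points for endpoint 1.

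The 5% guarantee of either procedure assumes one pre-specified test per endpoint. Primary outcome measures lists three time points for deterioration and two tumour components for residual volume, and the study has three arms. Moving from Bonferroni to Holm does not settle which single test represents each endpoint.

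**What to change.** Before outcome data are examined, replace weighted Bonferroni by weighted Holm (weights 0.8/0.2) in Sample size and in Primary study parameters. Suggested wording: endpoint 1 is tested at 4% and endpoint 2 at 1%; if either is significant, the other is tested at 5%. In the same place, name the one test per endpoint to which this applies.

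Report 96% and 99% intervals alongside the tests, and state that they may not match the Holm decision exactly when the second endpoint is significant only at 5%.

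The cost is one or two sentences and slightly less tidy intervals; no patients or procedures are added. The change should not be used to justify or reduce the figure of 411.

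### The 137 per arm gives 80% power for neurological deterioration only as an unstated one-sided test of control against both mapping arms pooled, while the second endpoint's 94 per arm is two-sided and arm against arm; the 88% is also wrong

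*Protocol article*

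**What the plan says.** The Sample size section splits a 5% error rate over two primary endpoints by weighted Bonferroni, 4% and 1%.

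- **Endpoint 1**, neurological deterioration at 6 weeks: 10% without mapping and 3% in each mapping arm. A two-sample test of proportions with continuity correction "requires 411 patients (137 per arm) in total in order to detect the above-mentioned difference of 7% with 80% power" at the 4% level.
- **Endpoint 2**, no residual contrast-enhancing tumour: 25% versus 50%. The same kind of test "requires 188 patients (94 per arm) in total", for a "difference of 25% with 80% power at a 1% significance level".
- The larger number governs, and 411 evaluable patients are said to "allow the difference of 25% in proportion of patients without residual tumour to be detected with 88% power".
- After a 10% allowance for ineligibility and withdrawal, "a total of 453 patients will be included (151 patients per arm").

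Primary study parameters then specifies a logistic model for endpoint 1 in which "the treatment arm effect will be tested at 4% significance level", and a test of the group effect at 1% for endpoint 2. Neither section says whether the tests are one- or two-sided, or whether the two mapping arms are pooled.

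**The concern.** The ingredients for endpoint 1 are fully listed: test, correction, two rates, power and level. A reader who puts them into the usual two-sided, arm-against-arm formula gets 235 per arm, not 137. The figure for endpoint 2, taken from the same kind of formula two sentences later, does come out on that usual basis. So one paragraph appears to use two different conventions without saying so.

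At stake is the power of the neurological-safety endpoint, which sets the size of the study. If the analysis is two-sided, or compares each mapping technique with no mapping, the chance of missing the assumed effect is larger than the 20% that the article implies. A null result could then be read as stronger evidence than it is.

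**Working it through.** **Inputs** (all from Sample size; 1:1:1 allocation from Study design). Endpoint 1: p1 = 0.10, p2 = 0.03, d = 0.07, level 4%. Endpoint 2: p1 = 0.25, p2 = 0.50, d = 0.25, level 1%. Power 80%, z = 0.8416. Let k be the number of mapping patients per control: 1 for one arm versus control, 2 for both mapping arms pooled.

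**Formulas** (pooled variance, continuity-corrected), with p̄ = (p1 + k·p2)/(1 + k):

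- A = zα·√[(1 + 1/k)·p̄(1 − p̄)] and S = √[p1(1 − p1) + p2(1 − p2)/k]
- Controls without correction: n0 = (A + 0.8416·S)²/d²
- Controls with correction: n = (n0/4)·[1 + √(1 + 2(k + 1)/(n0·k·d))]²
- Corrected power at n controls: √n0 = [n − (k + 1)/(2kd)]/√n, then power = Φ[(d·√n0 − A)/S]

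**Step 1. Reproduce 137 (endpoint 1, 4%, corrected).**

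| Sidedness | Comparison | n0 | Controls n | Total |
|---|---|---|---|---|
| two-sided | one arm vs control | 206.7 | 234.4 → 235 | 470 (705 over three arms) |
| one-sided | one arm vs control | 165.6 | 193.1 → 194 | 388 (582 over three arms) |
| two-sided | pooled vs control | 143.1 | 163.8 → 164 | 492 |
| one-sided | pooled vs control | 116.0 | 136.6 → 137 | 137 + 274 = 411 |

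Only the last row gives 137 and 411. In that row zα = 1.7507, p̄ = 0.0533, A = 0.4818 and S = 0.3233.

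**Step 2. Reproduce 94 (endpoint 2, 1%, corrected).** Two-sided, one arm vs control: n0 = 86.1, n = 93.97 → 94 per arm, 188 for two arms. One-sided, one arm vs control gives 82 per arm. Pooled gives 72 controls two-sided and 63 one-sided. Only the two-sided, arm-against-arm version gives 94.

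**Step 3. Power of endpoint 1 at 137 controls, 4%.**

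- Pooled, one-sided, corrected: √n0 = (137 − 10.714)/11.705 = 10.789; (0.7553 − 0.4818)/0.3233 = 0.846; power 80.1%. This is the article's 80%.
- Pooled, two-sided, corrected: (0.7553 − 0.5652)/0.3233 = 0.588; power 72.2%. Uncorrected, with √n0 = 11.705: 78.4%.
- One arm vs control, two-sided, corrected: √n0 = (137 − 14.286)/11.705 = 10.484; (0.7339 − 0.7160)/0.3451 = 0.052; power 52.1%. Uncorrected: 61.8%. Likelihood-ratio test, 400,000 simulated trials: 65%.

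**Step 4. Power of endpoint 2 at 137 controls, two-sided 1%, corrected.**

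- One arm vs control: √n0 = (137 − 4)/11.705 = 11.363; (2.8407 − 1.7635)/0.6614 = 1.629; power 94.8%.
- Pooled: √n0 = (137 − 3)/11.705 = 11.448; (2.8621 − 1.5553)/0.5590 = 2.338; power 99.0%.

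The stated 88% corresponds to about 111 per arm (87.9%), not 137.

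**Step 5. The inflated number.** 411 × 1.10 = 452.1, and 137 × 1.10 = 150.7 → 151 per arm, so 453 reproduces. A 10% loss from 453 leaves 407.7; dividing instead, 411/0.9 = 456.7 → 457.

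**The case against.** **Pooling may well be what was meant.** The Sample size section gives arms 1 and 2 one common rate as the experimental groups, and the rule that allots the first ten events to the arm effect fits a single arm parameter. On that reading the two-sided shortfall is 2 to 8 points (78% or 72% against 80%), not the gap seen for a single arm. This stands, and the pooled figure should be read first. It does not rescue the text, because the 80% also needs a one-sided test that is nowhere stated, and 78% requires dropping the continuity correction that the article specifies.

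**The total of 188 could be on the same basis as 411.** A one-sided pooled calculation gives 62.1 controls and 124.2 mapping patients, which round up to 63 + 125 = 188. But the article says 94 per arm, which fits only the two-sided, two-arm version. If the pooled basis was intended, the per-arm figure is wrong instead, and the paragraph still needs correcting.

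**The 88% harms nobody.** True: it understates the power and changes no decision about size. It is still a stated figure that does not follow from its inputs.

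**Stronger readings that the document does not support.**

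- A reader might infer that the promise that "the overall type I error rate does not exceed 5%, we apply a weighted Bonferroni correction for multiple testing" fails, because one-sided 4% corresponds to two-sided 8%. It does not fail: a one-sided test at 4% has a type I error of 4%, and 4% + 1% is 5%. Sidedness affects power and direction here, not the level.
- A reader might add an inflated family error from testing each mapping arm against control at 4%. The analysis section describes one test of the arm effect, not two pairwise tests.
- A reader might fault the power for awake versus asleep mapping. The Discussion mentions that comparison, but no power is claimed for it.
- A reader might say that 453 does not reproduce. It does, as 411 × 1.10.

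**Conclusion.** The sample-size paragraph is wrong as written. With the stated correction, a "difference of 7% with 80% power at a 4% significance level" is met at 137 per arm only by a one-sided test of pooled mapping versus control. No two-sided, continuity-corrected comparison reaches 80%: it is 72% pooled and 52% for one arm. Less conservative tests give 78% pooled and up to 65% for one arm. Endpoint 2, with its stated 94 per arm, is sized two-sided and arm against arm, and its power at 137 per arm is about 95% (99% pooled), not 88%.

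These figures rest on the article's own rates, on 137 evaluable patients in every arm, and on unadjusted tests. The covariate-adjusted logistic model could differ somewhat. The conclusion is not that the study is invalid or that its error rate is uncontrolled. It is that the stated power belongs to a test the article does not name, and that the two primary endpoints do not share a stated basis. The 453 is a minor matter: about 408 evaluable patients instead of 411 if the loss is 10% of those enrolled.

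**What to change.** 1. State the sidedness and the primary contrast in both Sample size and Primary study parameters, the same for both endpoints. The choice of contrast is the sponsor's. It should take into account that, under Study design, speech-eloquent tumours enter only the awake and no-mapping arms, so pooling combines arms with a different case mix.
2. Restate the endpoint 1 power at 411 for that contrast: two-sided, 72% to 78% for pooled mapping versus none, or 52% to 65% for one mapping arm versus none. If the one-sided pooled test is what was intended, say so; the 80% then stands.
3. Replace 88% to match: 95% (one arm versus control) or 99% (pooled), two-sided. Make the 94 per arm agree with the chosen basis.
4. Minor: say that 453 enrolled gives about 408 evaluable after a 10% loss, or that 411 evaluable would need 457.

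The cost is rewording two paragraphs and, under a two-sided test, a less favourable stated power for endpoint 1. Items 1 to 3 need no extra patients.
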